### 2) THE NUMBER OF PARTICIPNATS

The following are assumed to calculate the sample size.

- A. Level of significance,  $\alpha=0.0167$
- B. The ratio of the treatment and control group = 1:1:1
- C. Power of the test,  $1-\beta = 80\%$
- D. In a previous study, we estimated that the proportions of patients with immediate resolution in PC-BPPV would 70% in the treatment groups, and 38% in the sham group.
- E. The formula for calculating the number of samples and the calculation results are as follows.
  - i.  $n1=n2=[Z_{\alpha/2} \sqrt{2\bar{P}(1-\bar{P})} + Z_{\beta}\sqrt{P_1(1-P_1)+P_2(1-P_2)}]^2 / (P_1-P_2)^2$
  - ii.  $n1$ = Sample size in the control group
  - iii.  $n2$ = Sample size in the treatment group

- iv.  $p_1, p_2$  = Expected outcome rates for each group
- G. Based on these estimations, a sample size of 159 participants is obtained with a dropout rate of 5%.
- H. The calculated sample size considers the drop rate, and in actual clinical research, more or fewer participants may be required than the calculated number of study subjects. When 30%, 60%, or 90% of the expected study subjects are achieved, a Data and Safety Monitoring Board meeting will be held to determine whether the number of participants is appropriate.

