BPPV was traditionally considered as a benign condition that often resolved spontaneously over time without specific treatment. On average, PC-BPPV resolved about 39 days later. However, for the effective management of BPPV and to alleviate dizziness, accurate diagnosis and canalith repositioning maneuvers (CPM) are recommended.

Previous randomized controlled trials have proven that head-shaking and mastoid oscillation maneuvers effectively treat cupulolithiasis of the horizontal canal benign paroxysmal positional vertigo (HC-BPPV-cu). However, no data exist regarding the therapeutic efficacy of these maneuvers in PC-BPPV-cu.

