## **5) TRIAL ENDPOINTS**

- A. Primary endpoint: The overall short-term resolution rate of positional vertigo and nystagmus in the following day.
- B. Secondary endpoint: The immediate efficacy of two trials of each maneuver within 30 minutes.

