## 8. STATISTICS

### 1) DESCRIPTION OF STATICS METHODS

The demographic distribution of study participants by treatment maneuvers were compared using the Chi-squared test and one-way analyses of variance (ANOVA). If the results of the Chi-squared test were significant, additional post-hoc tests were performed using Bonferroni adjusted alpha level of 0.0167 per test (0.05/3). Statistical analyses were performed using SPSS (version 27.0; SPSS, Chicago, IL, USA).

The primary outcome was analyzed using both intention to-treat and per-protocol methods. Patients who did not complete the assessment in the following day were excluded from the per-protocol analysis.

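### The 159-patient sample size and its 80% power are derived for immediate resolution, the secondary endpoint; power for the next-day primary endpoint is not established

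*Protocol*

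**What the plan says.** Protocol section 7, Trial endpoints, item A: "Primary endpoint: The overall short-term resolution rate of positional vertigo and nystagmus in the following day". Item B: "Secondary endpoint: The immediate efficacy of two trials of each maneuver within 30 minutes".

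Protocol section 8, subsection 2 (number of participants), item D: "we estimated that the proportions of patients with immediate resolution in PC-BPPV would 70% in the treatment groups, and 38% in the sham group". The other inputs in that subsection are a significance level of 0.0167, 1:1:1 allocation, 80% power, a pooled two-proportion formula using the two-sided critical value, and 5% dropout. The result is 159, which the study summary gives as 53 per arm. Item H adds monitoring board meetings at 30%, 60% and 90% of accrual to consider whether the number is appropriate.

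Section 8, subsection 1 ties 0.0167 to the pairwise tests: "Bonferroni adjusted alpha level of 0.0167 per test (0.05/3)". It also removes patients without the next-day assessment from the per-protocol analysis of the primary outcome, which confirms that the primary outcome is the next-day one.

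Section 7, Study methods, item E and the study procedures table show that only patients still symptomatic after V1 come back for V2, and that no maneuver is given between the end of V1 and the V2 assessment.

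**The concern.** A sample-size calculation supports the endpoint whose rates go into it. Here the rates are for immediate resolution, while the trial will be judged on next-day resolution. The protocol neither assumes a next-day rate nor says that the immediate rates serve as a proxy.

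The two quantities are related but not the same. Patients resolved at V1 are not called back, so the overall next-day rate is most naturally V1 resolution plus whatever resolves overnight. The two coincide only if overnight resolution is zero in every arm. What is at stake is the 80% power claim for the primary comparison. As written, nobody can tell what power 159 patients give for it.

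**Working it through.** **Inputs.** From section 8, subsection 2: p(treated) = 0.70, p(sham) = 0.38, two-sided alpha 0.0167, power 80%, dropout 5%, three equal arms. Normal quantiles: z(alpha/2) = 2.393, z(beta) = 0.842.

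**Step 1: reproduce 159.** With mean proportion (0.70 + 0.38)/2 = 0.54:

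- First term: 2.393 × √(2 × 0.54 × 0.46) = 2.393 × 0.7048 = 1.687
- Second term: 0.842 × √(0.70 × 0.30 + 0.38 × 0.62) = 0.842 × 0.6675 = 0.562
- n = (1.687 + 0.562)² / 0.32² = 49.38, so 50 per arm
- 50 / 0.95 = 52.6, so 53 per arm; 3 × 53 = 159

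This matches the protocol exactly. Inverting the same formula at 50 evaluable per arm gives 80.6% power. So 159 and 80% both follow from the immediate-resolution rates.

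**Step 2: carry the rates to the next day.** Let r(t) and r(s) be the fractions of patients unresolved at V1 who resolve overnight in a treated arm and in sham. Count V1 successes as still resolved, since they are not recalled. Then:

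- next-day treated rate = 0.70 + 0.30 r(t)
- next-day sham rate = 0.38 + 0.62 r(s)
- gap = 0.32 + 0.30 r(t) − 0.62 r(s)

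With a common fraction r, the gap is 0.32 × (1 − r), because sham has more unresolved patients to gain from. With different fractions it can narrow, hold or widen.

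**Step 3: power for the next-day endpoint** (same formula, 50 evaluable per arm, alpha 0.0167). The fractions below are assumptions. Only 1/39 has a link to the protocol: the Background gives about 39 days to resolution on average for PC-BPPV, read here as a constant daily rate.

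| Assumption | Treated | Sham | Gap (points) | Power |
|---|---|---|---|---|
| No overnight resolution | 70.0% | 38.0% | 32.0 | 81% |
| Equal, r = 1/39 | 70.8% | 39.6% | 31.2 | 78% |
| Equal, r = 10% | 73.0% | 44.2% | 28.8 | 71% |
| Equal, r = 20% | 76.0% | 50.4% | 25.6 | 61% |
| Equal, r = 30% | 79.0% | 56.6% | 22.4 | 50% |
| Unequal, 20% treated, 10% sham | 76.0% | 44.2% | 31.8 | 82% |
| 32-point gap kept at higher rates | 82.0% | 50.0% | 32.0 | 85% |

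In the unequal row the gap is marginally smaller than 32 points, yet power is slightly higher, because the rates have moved away from 50% and the variance is lower.

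**The case against.** The strongest reply is that the endpoints are nested. Immediate resolution is the main component of the next-day rate, so using it for planning is defensible, and where the Background says "no data exist regarding the therapeutic efficacy of these maneuvers in PC-BPPV-cu", borrowing rates is normal practice. That stands as a reason why a proxy could be acceptable. It does not help as written, because the protocol never says that a proxy is being used or why.

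A reader might infer that the trial is underpowered. The documents do not support this. Loss of power requires overnight resolution to be about equal across arms, or higher in sham, and no overnight fraction is stated anywhere. The one figure with a link to the protocol costs about 2 points (78% against 81%), and the last two rows of the table keep or raise power.

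A reader might also take the wording of the secondary endpoint, "The immediate efficacy of two trials of each maneuver within 30 minutes", to show that the 70% and 38% are mis-timed, since Study methods places a 30-minute wait after each of two maneuvers. The phrase can mean 30 minutes after each maneuver. It is loose wording and does not change the sample size. Even if the rates were one-maneuver rates with independent repeats, two maneuvers would give 1 − 0.30² = 91% vs 1 − 0.62² = 62%, with power of 87%.

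Finally, the board meetings at 30%, 60% and 90% might catch a wrong assumption. They mitigate little, because no rule is given and there is no next-day assumption to check against.

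**Conclusion.** The point holds as a mismatch between the endpoint used for sizing and the primary endpoint. The calculation is correct for what it computes, but the stated 80% is the power for immediate resolution and is not established for next-day resolution.

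The size and sign of the discrepancy depend on rates that the protocol does not give. Over the assumptions tabulated, power for the primary endpoint runs from 50% to 85%. The range rests on 50 evaluable patients per arm, two-sided alpha 0.0167, and reading the primary endpoint as cumulative. The conclusion that power is unestablished needs none of the assumed overnight fractions. A claim that power is too low would need them.

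**What to change.** In section 8, subsection 2, item D, state the assumed next-day resolution rate for each arm and its basis; or state that the immediate rates are used as a proxy for the next-day rates, and why. Then restate the power of 159 patients for the next-day primary endpoint, with a range that shows scenarios on both sides of 80%, and label the existing 80% as the power for immediate resolution.

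Keep the primary endpoint. Exchanging it with the secondary so that it fits the calculation would change the trial's main question, which this mismatch does not require.

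The cost is an amendment to one item of text. The downside is that the stated power may become less favourable. If the sponsor's own next-day rates put it well below 80%, whether 159 is still acceptable becomes a separate decision to be made openly.

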### **3) THE LEVEL OF STATISTICAL SIGNIFICANCE**

$P < 0.05$

### **4) PROCEDURE FOR ACCOUNTING FOR MISSING, UNUSED, AND SUPURIOUS DATA**

Missing values in parameters will be imputed with the Last Observation Carried forward.

### **5) INCLUSION IN ANALYSIS**

The primary outcome would be analyzed using both intention-to-treat and per-protocol methods. Patients who can not successfully use the web-based system will be excluded from the per-protocol analysis.

### **6) PROCEDURE FOR REPORTING ANY DEVIATIONS FROM THE ORIGINAL STATISTICAL PLAN**

This process will be conducted with a guidance of an IDMC responsible for monitoring safety and effect during the trial. The final study protocol and informed consent will be reviewed and approved by the corresponding health authorities and ethics

boards/institutional review boards for all participating study sites.

### **B. Items**

- i. study accruals: essential documents, ICF (informed consent form), CRF (case report form)
- ii. safety: encryption of data, appropriateness of data management, contrast source documents and study documents

### **C. Methods and interval**

- i. The independent data monitoring committee (IDMC) regular review is once a year.
- ii. When 30% of the expected study subjects are recruited, an IDMC meeting will be held.
- iii. Every time a serious adverse event occurs, or when the monitoring manager deems it necessary, an irregular review will be held.

### **D. Reporting of adverse events, non-compliance, and reporting of unexpected problems**

- i. Adverse events, unexpected problems, and non-compliance with the protocol found according to the monitoring results will be reported to the IRB within 15 working days after becoming aware of the details.

### **E. Criteria for study discontinuation**

: This study will be stopped under the following conditions

- i. When the target number of study subjects has been reached.
- ii. Cases where unexpected serious adverse events discovered during the study are continuously reported.

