| Safety evaluation    | Not applicable                                                                                                                                                                                                                                                                                                                                                    |
| Visit schedule       | Subjects will be scheduled to return to the clinic the next day if the vertigo and nystagmus will not resolve after two randomized maneuvers on the day of the visit.                                                                                                                                                                                             |
| Statistical analysis | Any difference in the treatment response would be determined using ANOVA and Chi-square test between the treatments and control groups.                                                                                                                                                                                                                           |
| Expected effects     | The head shaking and mastoid oscillation maneuvers would be recommended as initial treatment options for PC-BPPV-cu.                                                                                                                                                                                                                                              |

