## ▪ STUDY PROCEDURES

| Study procedure                     | V1              |               | V2 (V1+1day)                                                  |               |
|-------------------------------------|-----------------|---------------|---------------------------------------------------------------|---------------|
|                                     | Treatment group | Control group | Treatment group                                               | Control group |
|                                     |                 |               | When the subjects still have positional vertigo and nystagmus |               |
| Informed consent                    | X               | X             |                                                               |               |
| Demographics assessment             | X               | X             |                                                               |               |
| Inclusion/exclusion criteria        | X               | X             |                                                               |               |
| Medical history                     | X               | X             |                                                               |               |
| Assessment of dizziness history     | X               | X             |                                                               |               |
| Neuro-otological examinations       | X               | X             |                                                               |               |
| Positional test                     | X               | X             | X                                                             | X             |
| Canalith repositioning maneuver     | X               | X             |                                                               |               |
| Determination of treatment response | X               | X             | X                                                             | X             |
| End of study                        |                 |               | X                                                             | X             |

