## **6) BENEFITS AND RISK FOR THE PARTICIPANTS**

- A. By participating in this study, it will be possible to save time and medical expenses by immediate treatments. Even when symptoms persist, subjects will be allowed to visit the hospital the next day and receive treatment, which is a faster process than using the general treatment system. Therefore, there are no anticipated risks from participation in this study.
- B. Subjects who visit the hospital due to persistent symptoms will receive a video-oculography test. The study team will be responsible for the medical fees of video-oculography.

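### The protocol marks safety evaluation as not applicable and schedules no adverse-event recording, so its safety review, IRB reporting and stopping rules rest on unsystematic, probably incomplete capture

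*Protocol*

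**What the plan says.** The Protocol speaks in two ways about harm.

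**Sections that plan no safety data**
- Study Summary: "Safety evaluation | Not applicable".
- Study Procedures table: ten rows, from consent to end of study. Efficacy has its own row, "Determination of treatment response", at both visits. No row concerns adverse events.
- Section 7, Benefits and Risk for the Participants: "there are no anticipated risks from participation in this study".
- Monitoring, B. Items: the item labelled as safety reads "safety: encryption of data, appropriateness of data management" and goes on to the checking of source against study documents. Harm to participants is not listed.

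**Sections that use safety data**
- Section 8, item 6 (deviations from the statistical plan): the IDMC is responsible for monitoring safety as well as effect.
- Monitoring, C. Methods and interval: an irregular review is held "Every time a serious adverse event occurs".
- Monitoring, D: adverse events found through monitoring are reported to the IRB within 15 working days of awareness.
- Monitoring, E. Criteria for study discontinuation: "Cases where unexpected serious adverse events discovered during the study are continuously reported".

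**Who is seen after day 1.** The summary says: "Subjects will be scheduled to return to the clinic the next day if the vertigo and nystagmus will not resolve after two randomized maneuvers". The V2 columns of the procedure table carry the same condition: "When the subjects still have positional vertigo and nystagmus".

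**The concern.** Four rules (IDMC safety monitoring, irregular review, IRB reporting, stopping) take adverse events as input, while the summary and schedule plan no step that records them. A site that follows the schedule exactly would pass on only what a participant happens to mention or an investigator happens to notice. The yearly IDMC review and the review at 30% recruitment would take place, but without planned safety data to examine.

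Two things are at stake. The first is timely recognition of harm. The second is the conclusion: the summary expects both maneuvers to be recommended as initial treatment, and the plan would provide no systematic comparison of tolerability with sham. The only contact after day 1 depends on treatment response, so events that surface there would not be comparable between arms.

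**Working it through.** **1. The plan's own figure.** Section 8, The Number of Participants, gives two-sided alpha 0.0167, power 80%, rates 70% and 38%, and 5% dropout. With mean rate 0.54:

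n = [2.393 × √(2 × 0.54 × 0.46) + 0.842 × √(0.70 × 0.30 + 0.38 × 0.62)]² / 0.32² ≈ 49.4, rounded up to 50 per arm.

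50 / 0.95 = 52.6, rounded up to 53; 3 × 53 = 159. The stated total reproduces. It is used below only for the denominators: 106 active (2 × 53) and 53 sham.

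**2. Rules against data sources**

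| Rule | What it needs | Planned source |
|---|---|---|
| IDMC monitors safety (Section 8, item 6) | Safety data | None in the schedule |
| Irregular review (C. iii) | A serious event becoming known, or the monitoring manager's judgement | None for the event |
| Report to IRB (D) | Events found by monitoring | Monitoring can find only what was recorded; no row records events |
| Stop (E. ii) | Repeated unexpected serious events | None |
| Yearly and 30% reviews (C. i, ii) | Calendar or recruitment | Not triggered by events |

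**3. Next-day observation by arm.** Assumptions: the 70% and 38% immediate resolution rates apply after the day-1 maneuvers, and every unresolved participant returns.

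- Active: resolved 0.70 × 106 = 74.2; returning 106 − 74.2 = 31.8, or 30%.
- Sham: resolved 0.38 × 53 = 20.1; returning 53 − 20.1 = 32.9, or 62%.
- No planned contact after day 1: 74.2 + 20.1 = 94.3 of 159, or 59%.

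Suppose next-day events had the same true rate r in all arms, unrelated to resolution, and were picked up only at V2. The rates per randomized participant would then be 0.30r (active) and 0.62r (sham), a ratio of 0.30 / 0.62 = 0.48. The active maneuvers would appear to have about half the event rate of sham with no true difference. Volunteered reports from responders would soften this by an unknown amount.

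**4. What systematic questioning would support.** With zero events among n people asked, the one-sided 95% upper bound is 1 − 0.05^(1/n):

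- n = 106: 1 − 0.05^(1/106) = 2.8%
- n = 53: 1 − 0.05^(1/53) = 5.5%

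With 50 per arm assessed, the bounds are 3.0% (n = 100) and 5.8% (n = 50). These figures show what the fix would provide. They do not estimate how many events the present plan would miss.

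**The case against.** A reader might infer that the safety rules cannot operate at all, or that events in day-1 responders are bound to be lost. The documents do not support that. Irregular review, IRB reporting and the stopping condition all act on events once known, however they come to light. Participants are re-examined 30 minutes after the first maneuver and, if it was repeated, 30 minutes after the second. Section 9, Consent Process, gives every participant the researcher's contact information. Section 9, Research Ethics, commits researchers to good clinical practice. Capture is unsystematic, not absent.

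A reader might also infer that all IDMC reviews depend on adverse events. Only the irregular review has that trigger, and the text does not name the body that holds it. Nor does the wording of B. Items confine the IDMC to data handling, because Section 8, item 6 gives it safety as well. The opening of the monitoring section was not in the text available, so who applies list B is left open here.

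It can further be said that a trial may lack a formal safety endpoint and still report serious events, and that tabulation by arm belongs in a SAP. Both are fair. But whether events are recorded, and at which visit, is settled in the protocol's summary and schedule, and these conflict with its own later sections. No analysis plan can tabulate what was not collected.

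Two practical objections also stand, and they shape the fix. A question at V2 does not reach day-1 responders. A question about the effects of the maneuver, put by the blinded assessor, could reveal the arm.

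**Conclusion.** The contradiction is on the face of the protocol. The Study Summary, the Study Procedures table and the monitoring items plan no recording of harm, while Section 8, item 6 and monitoring items C to E rely on it. The consequence is unsystematic, probably incomplete capture.

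Under the protocol's own rates, about 59% of participants would have no planned contact after day 1, and next-day observation would be about 30% in the active arms against 62% in sham. This assumes that the 70% and 38% rates hold for the day-1 maneuvers and that all unresolved participants attend. The conflict itself depends on no figure. It does not put the efficacy comparison or the sample size in doubt.

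**What to change.** Reconcile the Study Summary, Study Procedures table and monitoring item B with Section 8, item 6 and monitoring items C to E. In detail:

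- Replace the not-applicable entry with adverse-event recording, and add a row to the procedure table.
- Add one CRF line, with fixed wording, at each existing same-day post-maneuver contact and at V2.
- Have the unblinded treating physician ask it, or ask only after the blinded response has been recorded. The first option is safer at the first contact, because the same assessor may examine the participant again.
- Use the same-day answers to compare arms, since V2 attendance depends on response. Show the first 30-minute contact separately: it is the only one that every participant has, because the second follows only a repeated maneuver.
- Give the recorded events to the IDMC, including at its yearly and 30% reviews.

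**Cost:** one CRF line per contact and one table, with no added visit. Events after day 1 in responders would still be known only if volunteered, and the protocol should state this as a limitation. No change to a maneuver or to a stopping criterion is proposed here.
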